**Fig. 1 Fig1:**
[figure not shown]
Study Design. Physicians will be randomly assigned to 30-h CST program (*experimental group*) or to a waiting list (*control group*). Training efficacy is assessed in the context of an encounter with a simulated advanced stage cancer patient at baseline and after the CST for the experimental group, and after four months for the waiting list group. Communicational, psychological and physiological assessments will be conducted

### CST program

#### CST aims

The aim of the CST is to improve the ability of physicians to communicate about uncertainty and hope with cancer patients.

#### CST logistics

The CST is a manualized program comprised of ten 3-h sessions (30 h) spread over four to five months. Each training group will include three physicians. The training will be conducted at locations and times choosen by the physicians within each group. The trainer of the experimental group will be an experienced facilitator who will conduct all training sessions ([name]). The training timetable will not include more than two 3-h sessions in one day. Physicians will have the opportunity to register in groups of three or individually. In the latter case, physicians will be assigned to groups according to geographical proximity.

#### CST sessions

The first session of the training program will include a general introduction to training and a modeling session. Sessions two to four will focus on appropriate communication skills for addressing uncertainty and hope according to a model detailed in a training manual. During sessions five to seven, participants will learn to transfer their newly-learned skills to clinical practice. Finally, during sessions eight to ten, skills learned during the training program will be consolidated.

#### CST program

The CST program will include theoretical information giving about uncertainty and hope in cancer care (based on psychodynamic, cognitive-behavioral and systemic theories), modeling and role-playing.

##### Theoretical information giving.

The CST trainer will provide theoretical information on communication skills needed to address uncertainty and hope in encounters with cancer patients. These skills will focus on assessing patient expectations about the future and restructuring patient understandings with appropriate information when needed; and assessing patient hopes about the future and supporting those which are realistic [47]. All skills will be based on a collaborative and bidirectional communication process between physicians and patients on topics such as disease prognosis or expected and unexpected medical, psychological and social effects of cancer treatments. A specific algorithmic theoretical model has been designed to aid physicians in the implementation of these communication skills.

##### Modeling.

During the first CST session, physicians will observe a 16-min video of a simulated interview in which the trainer acts as a physician communicating with a patient suffering from ﻿﻿an ﻿advanced cervical cancer. In the scenario, the patient has come for chemotherapy treatment and is requesting reassurance about treatment efficacy.

The modeling session will emphasize three factors: 1) physician attitudes necessary to address uncertainty and hope, 2) patient’s reactions to the discussion of uncertainty and hope and 3) the need to set up a safe and comfortable setting in which to model communication skills needed to address uncertainty and hope. After the video, physicians will be given one hour to debrief and react to the simulated interview.

##### Role-playing.

Throughout training, participants will be invited to participate in interactive role-playing with immediate and circular feed-backs [48]. Physicians will be asked to identify a clinical situation for the focus of the role-play situation. In session two to four, physicians will be asked to define a situation that would be highly uncomfortable in terms of uncertainty and hope management. In training sessions five to seven, physicians will be asked to identify clinical situations in which the transfer of learned communication skills would be difficult. Finally, in training sessions eight to ten, physicians will be asked to identify clinical situations during which the transfer of acquired skills would be uncomfortable.

During role-play, the physician who reports the clinical situation will take on the role of the patient. This will allow role-play to be as realistic as possible. The small group context will promote an interactive session. During role-play, the “patient” will be exposed to the ways that he and his two colleagues are communicating in repeated rotations. During each rotation, the facilitator will suggest alternative strategies that were taught in the theoretical model and shown in the modeling video.

##### Transferring to clinical practice.

Each training session will start with a 15-min summary of material learned since the beginning of the training program along with a debriefing from participants of attempts to transfer the learned skills to their clinical practice. Each training session will end with a 10-min summary of the skills learned during the session, the difficulties that may have been encountered, and a proposal for the transfer of newly learned skills to future encounters with patients.

### Assessment procedure

The performance status, disease status and communication skills among cancer patients vary widely and as such, the use of standardized encounters with simulated patients has been recommended to assess the efficacy of CST programs designed for healthcare professionals [49]. The assessment procedure for the current study will involve the video recording of an encounter between the participating physician and a simulated advanced stage cancer patient. Participating physicians will be assessed individually. An investigator, not involved in the training program, will present each subject with questionnaires. The assessment procedure (Fig. 2) will include 7 steps: (1) continuous monitoring of heart rate, (2) relaxation exercise, (3) administration of questionnaires, (4) review of the simulated cancer patient medical chart, (5) administration of the second set of questionnaires, (6) encounter with the simulated cancer patient and (7) final set of questionnaires. Perceived stress will be measured seven times throughout the assessment procedure.

**Fig. 2 Fig2:**
[figure not shown]
The seven steps of the assessment procedure: 1) continuous monitoring of heart rate, (2) relaxation exercise, (3) administration of questionnaires, (4) review of the simulated cancer patient medical chart, (5) administration of the second set of questionnaires, (6) encounter with the simulated cancer patient and (7) final set of questionnaires. Perceived stress will be measured seven times throughout the assessment procedure

#### Simulated patient encounter

The simulated patient case was written by an oncologist and a psycho-oncologist at the medical oncology unit and the psycho-oncology clinic at the Jules Bordet Institute, Cancer Center of the Université Libre de Bruxelles. The simulated patient case was developed to increase physician uncertainty about predefined medico-psycho-social components and available evidence-based treatments. The simulated patient is a 36-year-old woman with advanced cancer. She is facing a third recurrence (hepatic metastasis) of a breast cancer that had previously been treated with surgery, hormone therapy, radiation therapy and chemotherapy. She has agreed to start a new chemotherapy treatment. The scenario specifies that the patient has requested a meeting with a physician to help her cope with her treatment decision. Participants will be instructed to address and respond to the concerns of the simulated patient and to take the time they need for doing that. The simulated patient will be played by an actress experienced in simulated patient encounters and will be trained to maintain a standardized script and behavior. Regular feedback sessions will be held to help the actress maintain reproducibility [50]. The simulated patient encounters will take place at the Communication Laboratory (LabComm) of the Centre de Psycho-Oncologie (Brussels, Belgium).

#### Psychological assessments

Participating physicians will be asked to complete a set of psychological questionnaires prior to reading the patient medical chart. Data on socioprofessional characteristics, practices in oncology and sense of mastery of the communication skills needed to address uncertainty and hope with cancer patients will be collected. A second set of psychological questionnaires administered immediately prior to the encounter with the simulated patient will gather information on the perceived realism of the medical chart of the simulated patient, agreement with the treatment decision, outcome expectancies on the medical, psychological and social status of the simulated patient, perceived uncertainty and hope regarding the medical, psychological and social outcomes of the simulated patient, and psychological reactions to uncertainty regarding the medical, psychological and social outcomes of the simulated patient. Finally, a third set of psychological questionnaires will be administered immediately after meeting with the simulated patient. These questions will assess to agreement with the treatment decision, satisfaction regarding the encounter with the simulated patient, and the sense of mastery regarding the communication skills used to address uncertainty and hope with the simulated patient. These psychological questionnaires will allow the assessment of predictors and correlates of communication skills learning used to address uncertainty and hope with the simulated patient.

#### Communication assessments

The encounter with the simulated patient will be video recorded and transcribed. Physician communication skills will be analyzed using three tools. The French communication content analysis software, LaComm (Centre de Psycho-Oncologie, Brussels, Belgium; http://www.lacomm.be/) analyzes verbal communication (in medicine in general and in oncology in particular) and identifies turns of speech and the type and content of speech. The explanation of how this software works has been detailed in previous publications [42, 51]. The Multidimensional analysis of Patient Outcome Predictions (MD.POP) is a reliable tool used to measure verbal expressions that address the clinical future of a patient during medical encounters. This coding system allows one to manually identify, code, and score detailed verbal content from a medical encounter transcript that addresses a patient’s clinical future. The detailed MD.POP codebook is available upon request. Finally, a specific interaction-process analysis system assessing communication skills addressing hope and uncertainty will be developed for the study [52].

#### Physiological assessments

Throughout all assessment procedures, physician heart rate will be monitored to assess the impact of the training program on the physiological arousal associated with communication about uncertainty and hope with the simulated patient. This assessment procedure has previously been used to measure the effect of CST on the physiological arousal of residents breaking bad news in a simulated task [53].

#### Statistical analyses

The primary outcome of the current study is the physicians’ increased communication performance after training during this encounter. A power analysis has been performed, based on a previous longitudinal study assessing physicians’ communication performance composite score in an encounter with a simulated advanced-stage cancer patient (Mean = 26; SD = 8) [54]. This power analysis was conducted considering 4 independent conditions according to the time (time 1 *versus* time 2) and the group (experimental *versus* control group). As there is no previous study assessing the efficacy of an intensive communication skills training program on physicians’ communication about uncertainty and hope, it was hypothesized that physicians in the control group will maintain a stable performance score from time 1 to time 2. It was also hypothesized that physicians in the experimental group will improve their performance score by 20% from time 1 to time 2. Sample size calculation has been based on an 80% power, a one-sided α = 0.05 t-test and an effect size of 0.65. Considering this power analysis, 60 evaluable physicians are therefore needed for the efficacy assessment. Considering a drop-out rate of 20%, 12 physicians should be moreover recruited (72 physicians in total). It should be recalled at this level that one trainer only will conduct the training of the experimental group. Secondary, to assess also the CST program efficacy, group-by-time effects will be performed using generalized estimating equation (GEE) on psychological, physiological and communicational assessments performed during the encounter with the simulated patient.

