**Methods/design:**

Physician participants will be randomly assigned in groups (*n* = 3/group) to a 30-h CST program (experimental group) or to a waiting list (control group). The training program will include learner-centered, skills-focused, practice-oriented techniques. Training efficacy is assessed in the context of an encounter with a simulated advanced stage cancer patient at baseline and after the CST for the experimental group, and after four months for the waiting-list group. Efficacy assessments will include communicational, psychological and physiological measures. Group-by-time effects will be analyzed using a generalized estimating equation (GEE). A power analysis indicated that a sample size of 60 (30 experimental and 30 control) participants will be sufficient to detect effects.

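### The stated 80% power belongs to a two-sample comparison at one time point; for the difference in change it depends on a baseline-to-post correlation that the independence wording sets to zero

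*Protocol article*

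**What the plan says.** All the sample-size inputs stand in the protocol article under Statistical analyses. A previous study supplies a mean of 26 and an SD of 8 for a composite performance score. On the structure: "This power analysis was conducted considering 4 independent conditions according to the time" and the group. On the hypotheses: "physicians in the control group will maintain a stable performance score from time 1 to time 2", while "physicians in the experimental group will improve their performance score by 20% from time 1 to time 2". On the calculation: "Sample size calculation has been based on an 80% power, a one-sided α = 0.05 t-test and an effect size of 0.65". The result is that "60 evaluable physicians are therefore needed for the efficacy assessment".

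The same section words the primary outcome as an increase in performance after training. It then introduces the group-by-time GEE as a secondary analysis.

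The abstract (Methods/design) names one analysis only: "Group-by-time effects will be analyzed using a generalized estimating equation (GEE)". The next sentence there gives the sample size: "a sample size of 60 (30 experimental and 30 control) participants will be sufficient to detect effects".

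Under Study design, each physician is assessed at baseline and again after training, or after four months on the waiting list.

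**The concern.** Three statements do not fit together.

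- The paragraph says that four independent conditions were considered, yet two of the four are the same trained physicians before and after, and the other two are the same control physicians before and after.
- The hypotheses describe a difference in change (+5.2 against 0), yet the standardised effect divides that change by the SD of a single score. No SD of change enters.
- The calculation is a single t-test. The main text does not say which contrast that test makes, and the abstract puts the 60 directly after the group-by-time GEE.

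A reader will therefore take the 80% as the power of the group-by-time effect. It may or may not be, depending on a correlation for which the only stated value is, in effect, zero. If the trial reports a null group-by-time result, the published power figure gives no firm basis for interpreting it.

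**Working it through.** **Inputs** (protocol article, Statistical analyses, unless noted): mean 26; SD 8; control change 0; trained change +20%; one-sided α 0.05; t-test; 80% power; 60 evaluable, split 30 and 30 in the abstract. The correlation ρ between a physician's two scores is not given. I take 0, 0.3, 0.5 and 0.7 as an assumed range, and assume the SD is 8 at both times.

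**Step 1: reproduce the plan's figure.**
- Change: 26 × 0.20 = 5.2 points.
- Effect size: 5.2 / 8 = 0.65, as stated.
- Two-sample t-test, 30 per arm, 58 df: noncentrality 0.65 × √(30/2) = 2.52; one-sided critical value 1.67; power 80.0%. With 29 per arm it is 78.8%.

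So 30 per arm is exactly the answer for two independent groups compared once, with a raw-score SD. A two-sided test would need 38 per arm (normal approximation), so the one-sided reading is the one used.

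**Step 2: the difference in change.** The SD of a change is 8 × √(2(1 − ρ)). At ρ = 0, which is what independence of the four conditions means, it is 8 × √2 = 11.31, and the effect size is 5.2 / 11.31 = 0.46. Equivalently, the variance of the contrast is 4 × 8²/30, twice that of the single comparison, which is 2 × 8²/30.

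**Step 3: a baseline-adjusted comparison of post-training scores.** The residual SD is 8 × √(1 − ρ²), used in the same t-test formula.

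| ρ | SD of change | Effect size | Power, difference in change | Residual SD | Power, baseline-adjusted |
|---|---|---|---|---|---|
| 0 | 11.31 | 0.46 | 55% | 8.00 | 80% |
| 0.3 | 9.47 | 0.55 | 68% | 7.63 | 83% |
| 0.5 | 8.00 | 0.65 | 80% | 6.93 | 89% |
| 0.7 | 6.20 | 0.84 | 94% | 5.71 | 97% |

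At ρ = 0 the change figure is 54.6% with 58 df and 55.0% if four separate cells give 116 df. At that correlation 60 per arm (120 in all) would be needed for 80%.

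The two definitions of the SD meet at ρ = 0.5, where 8 × √(2 × 0.5) = 8. Only there does the published effect size equal the effect size for change. Below 0.5 the 60 falls short for that contrast; above 0.5 it is more than enough.

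The baseline-adjusted column ignores the small cost of estimating the baseline slope, which takes the ρ = 0 figure to about 79.4%. It also makes no allowance for training in groups of three.

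**The case against.** The strongest reply is that the calculation is right for the test it names. Randomisation follows baseline, so expected baseline means are equal; with the control arm stable and the trained arm up 5.2, the expected difference at time 2 is also 5.2, and dividing by a cross-sectional SD of 8 is legitimate. The main text labels the group-by-time GEE secondary and nowhere claims 80% power for it. The four-conditions phrase may be loose wording for a two-by-two layout, and it does not enter the arithmetic.

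Much of this stands. The 60 is correct for a time-2 comparison, and there is no slip in the arithmetic. A missing correlation would by itself be a detail that an article may leave to the full protocol or analysis plan.

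It does not dispose of the point. The document nowhere names a time-2 comparison as the primary test. It words both the outcome and the hypotheses as change, and the abstract offers no analysis except the GEE. The published independence premise is wrong for repeated measures, whatever an analysis plan may add.

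A reader might go further and infer that the trial has only 55% power. The documents do not support that. The figure requires zero correlation between two scores from the same physician, which is the very premise criticised here, and it applies to a contrast that the main text calls secondary.

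**Conclusion.** The point holds in a limited form. The independence wording is wrong for this design, and the 80% is established only for a two-sample comparison of scores at one time point. For the difference in change, which the outcome and hypotheses describe and the abstract announces, power with 30 per arm runs from 55% at ρ = 0 to 94% at ρ = 0.7 and reaches the stated 80% at ρ = 0.5. These figures assume the plan's own 5.2-point effect, an SD of 8 at both times, one-sided 0.05, 60 evaluable physicians and no clustering by training trio; the values of ρ are mine. Severity is moderate, because a standard baseline-adjusted analysis makes the existing size adequate across the range. What needs correcting is which test the power figure belongs to.

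**What to change.** Keep 60 evaluable physicians. In Statistical analyses:

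1. Delete the reference to four independent conditions.
2. Name the primary test: a comparison of post-training scores between arms, adjusted for the baseline score (ANCOVA), with power of about 80% at ρ = 0 and 83%, 89% and 97% at 0.3, 0.5 and 0.7, before any allowance for training in trios.
3. Align the abstract, so that the sample-size sentence refers to that test and the group-by-time GEE is shown as secondary, as in the main text.

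If the group-by-time contrast is preferred as primary, state its power for an assumed baseline-to-post correlation, justify that value, and show the range in the table above.

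The cost is rewording a few sentences in the sample-size paragraph and the abstract. With the baseline-adjusted test, no further recruitment and no new measurements are needed. If the change contrast is kept and the correlation is thought to be below 0.5, the stated 80% would have to be lowered or the sample enlarged.

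### The 20% drop-out allowance is taken on the 60 evaluable physicians, so 72 recruits give about 58 evaluable at that rate, not 60; the consequence is small

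*Protocol article*

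**What the plan says.** The Statistical analyses section derives the sample size in three steps.

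- **Effect.** The reference composite score has mean 26 and SD 8. Controls are assumed to stay stable, while "physicians in the experimental group will improve their performance score by 20% from time 1 to time 2".
- **Evaluable number.** "Sample size calculation has been based on an 80% power, a one-sided α = 0.05 t-test and an effect size of 0.65". The section concludes that "60 evaluable physicians are therefore needed for the efficacy assessment". The Methods/design part of the abstract gives the split: "a sample size of 60 (30 experimental and 30 control) participants will be sufficient to detect effects".
- **Recruitment number.** "Considering a drop-out rate of 20%, 12 physicians should be moreover recruited (72 physicians in total").

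The CST logistics section adds that "Each training group will include three physicians", and the abstract says that physicians are randomised in such groups. Nothing in the article gives a second drop-out rate, defines the rate against completers, or provides for replacing physicians who leave.

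**The concern.** The requirement of 60 is stated as a number of evaluable physicians, so it must be what remains after loss. To have 60 left after a proportion has dropped out, the requirement is divided by one minus that proportion. The article instead multiplies 60 by 1.20. The three stated figures (60 evaluable, 20% drop-out, 72 recruited) therefore cannot all hold together.

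At stake is the recruitment target, which is the number the investigators will work to. If drop-out is as assumed, meeting the target still leaves the trial short of the number the article calls necessary. There is no slack in the 60 to absorb this: it is the smallest equal-arm total that reaches 80% power under the stated test.

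**Working it through.** **Inputs, all from the protocol article.** Mean 26, SD 8, improvement 20%, one-sided α = 0.05, t-test, power 80%, 60 evaluable, drop-out 20%, 72 recruited (Statistical analyses); 30 per arm (abstract); groups of three (CST logistics).

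**Step 1: reproduce the effect size.** 0.20 × 26 = 5.2 points; 5.2 / 8 = 0.65. This matches.

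**Step 2: reproduce the 60.** For a two-sample t-test with arms n₁ and n₂, power = P(T > t₀.₉₅,df), where T is noncentral t with df = n₁ + n₂ − 2 and noncentrality 0.65 / √(1/n₁ + 1/n₂). At 30 and 30, df = 58, the critical value is 1.672, the noncentrality is 2.517 and the power is 80.04%. At 29 and 29 it is 78.8%. So 30 per arm, 60 in all, is the minimum with equal arms, and the article's figure is reproduced.

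**Step 3: reproduce the 72.** 60 × (1 + 0.20) = 72. This is the only route from the stated figures to 72.

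**Step 4: apply the drop-out rate to the recruits.**

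- Expected evaluable from 72: 72 × (1 − 0.20) = 57.6, about 58.
- Recruits needed for 60: 60 / (1 − 0.20) = 75, which is 15 extra and not 12. Check: 75 × 0.80 = 60.
- Drop-out that 72 can absorb: (72 − 60) / 72 = 12/72 = 16.7%.

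**Step 5: power under the stated t-test** (effect size 0.65, one-sided α = 0.05).

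| Evaluable | Split | Power |
|---|---|---|
| 60 | 30/30 | 80.0% |
| 58 | 29/29 | 78.8% |
| 57 | 29/28 | 78.2% |

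The expected 57.6 lies between the last two rows, so the loss is 1.2 to 1.8 percentage points.

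**Step 6: does 75 work with groups of three?** 75 / 3 = 25 groups. Split 13 to 12, the arms are 39 and 36 recruits, with 39 × 0.80 = 31.2 and 36 × 0.80 = 28.8 expected evaluable. At 31 and 29, df = 58, the noncentrality is 2.516 and the power is 80.0%. The slight imbalance costs practically nothing.

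**The case against.** The best defence is that this hardly matters. The article gives no source for the 20%, and the effect size is a hypothesis, since by its own account no earlier study assessed this kind of training. A power difference of under two points is well within the uncertainty of those inputs. If actual drop-out is 16.7% or less, 72 delivers the 60. No estimate, test or conclusion changes. The number 72 is also convenient: 24 groups of three, 12 per arm. All of this stands, and it limits the weight of the point. It does not make the sentence correct, because the article states the rate, the requirement and the total itself, and they disagree.

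Three stronger readings are tempting, and the documents do not support them.

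- A reader might take the yield to be exactly 57. The expectation is 57.6, nearer to 58. Both fall short of 60, but the power should be given as the range 78–79%.
- A reader might argue that the target must be 78 (26 groups, 13 per arm) because training is in threes and the arms are equal, which would double the shortfall from 3 to 6. The article gives 30 and 30 for the sample size but states no rule that recruits must form equal numbers of groups per arm, and step 6 shows that 75 already restores the power.
- A reader might treat 78–79% as the power of the trial as a whole. It is power under the stated t-test only; the article gives no power figure for the GEE group-by-time analyses.

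**Conclusion.** The recruitment figure is wrong as written; the consequence is small. At the stated 20% drop-out, 72 recruits give an expected 57.6 evaluable physicians, a shortfall of 2.4 against 60. The correctly inflated target is 75, so the recruitment figure is 3 too low. Power under the stated test is then about 78–79% in place of 80%.

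This rests on three assumptions: that the 20% is a proportion of those recruited, which is the ordinary meaning and the only one the article offers; that drop-outs are not replaced, since no replacement is described; and that loss is about equal in the two arms. It accepts the 60 as the article derives it. It implies no bias and no fault in the analysis.

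**What to change.** Correct the sentence on drop-out in the Statistical analyses section in one of two ways.

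- **Keep 72.** State that it secures 60 evaluable physicians for drop-out up to 16.7%, and that at 20% drop-out about 58 are expected, with power of about 78–79% under the stated t-test. This costs one sentence and no further recruitment.
- **Raise the target to 75.** State that 15 physicians are added to the 60, forming 25 groups of three, and that a 13 to 12 split of groups keeps power at about 80%. This costs one sentence and three more physicians, that is, one more training group.

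Either is sufficient. If recruitment is already fixed at 72, the first is a complete correction.

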### Study design

Participating physicians will be randomly assigned to either the experimental group or the control group (Fig. 1). After baseline assessment, participants in the experimental group will attend a 4-month training program followed by a post assessment. Participants in the control group will be placed on a waiting list after baseline assessment and will be reassessed four months later. The process of randomization after baseline will allow for a double-blind assessment at baseline.

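### The named efficacy model, a group-by-time GEE, on its usual reading compares raw change between arms; adjusting for the pre-randomisation baseline score would be more precise at almost no cost

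*Protocol article*

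**What the plan says.** Under Statistical analyses, the article describes the primary outcome as improved communication performance in the simulated encounter. It then gives the sample size, and ends by saying that "group-by-time effects will be performed using generalized estimating equation (GEE) on psychological, physiological and communicational assessments". That last sentence is introduced as secondary. In the Abstract, the group-by-time GEE is the only analysis mentioned and carries no such label. The aim of the trial is likewise framed in terms of change over time. The only other test named anywhere is the one in the sample-size sentence: "one-sided α = 0.05 t-test and an effect size of 0.65".

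Under Study design, there is one assessment before allocation and one about four months later, and "The process of randomization after baseline will allow for a double-blind assessment at baseline". The baseline score is therefore a pre-randomisation measurement. Using it as a covariate, or constraining its mean to be equal across arms, is not mentioned.

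**The concern.** With two time points and the usual parameterisation (group, time, group by time), the interaction is the difference between arms in mean change. That model also estimates a baseline difference between arms, although randomisation makes the true difference zero. The full observed baseline difference is then subtracted from the post difference, whereas regression on baseline subtracts only rho times it.

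This matters in a trial of 60. With SD 8 and 30 per arm, the chance baseline difference has a standard error of 8 × sqrt(2/30) = 2.07 points, about 40% of the 5.2-point planning effect (2.07/5.2 = 0.40). If a difference of that size occurred and rho were 0.5, the change comparison would subtract 2.07 points and the adjusted comparison 1.03. On average over randomisations neither is biased, but the change comparison is noisier.

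**Working it through.** **Inputs from the article (Statistical analyses and Abstract).** Mean 26 and SD 8; the experimental group is expected to "improve their performance score by 20% from time 1 to time 2", while "physicians in the control group will maintain a stable performance score from time 1 to time 2". The effect is therefore 0.20 × 26 = 5.2 points, and 5.2/8 = 0.65, which matches "an effect size of 0.65". The power target is 80%, alpha is 0.05 one-sided, and there are 30 evaluable physicians per arm.

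**Input not in the article.** Rho, the correlation between the time 1 and time 2 scores. I take a range. The power statement itself says "This power analysis was conducted considering 4 independent conditions", so no correlation entered the calculation.

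**Step 1: reproduce the stated size.** A one-sided two-sample t-test with d = 0.65 needs 29.97 per arm, so 30 per arm and 60 in total. Power at 30 per arm is 80.0%. The noncentrality is 5.2 / (8 × sqrt(2/30)) = 5.2/2.066 = 2.517, on 58 df. The stated 60 is reproduced. It is the size for comparing single scores, because the SD of 8 is that of one score.

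**Step 2: variances.** Assume equal variances at both times and independent physicians. Per physician:

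- change: 2(1 − rho) × SD²
- post score adjusted for baseline: (1 − rho²) × SD²
- ratio, adjusted to change: (1 − rho²) / [2(1 − rho)] = (1 + rho)/2

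The ratio is below 1 for every rho below 1.

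**Step 3: power at 30 per arm.** Noncentral t, one-sided 0.05, with 58 df for change and 57 for the adjusted analysis. Example at rho 0.5: the SD of change is 8 × sqrt(1.0) = 8.00, noncentrality 2.517; the adjusted SD is 8 × sqrt(0.75) = 6.93, noncentrality 5.2 / (6.93 × sqrt(2/30)) = 2.907.

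| rho (assumed) | variance ratio | power, change | power, adjusted | total N for 80%, change | total N for 80%, adjusted |
|---|---|---|---|---|---|
| 0 | 0.50 | 54.6% | 80.0% | 118 | 60 |
| 0.3 | 0.65 | 67.6% | 83.2% | 82 | 54 |
| 0.5 | 0.75 | 80.0% | 89.0% | 60 | 44 |
| 0.7 | 0.85 | 94.1% | 96.7% | 36 | 30 |
| 0.8 | 0.90 | 98.9% | 99.4% | 24 | 22 |

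The N columns use the normal approximation. Simulation with 20,000 runs per value agrees: 67.8% and 82.3% at rho 0.3, 80.6% and 88.7% at 0.5, 94.3% and 96.6% at 0.7.

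**Step 4: allow for trios.** Physicians are randomised in groups of three, so 60 physicians form 20 trios. With an assumed intraclass correlation of 0.1, the design effect is 1 + (3 − 1) × 0.1 = 1.2. With 18 and 17 df, power for change and adjusted is about 59% and 75% (rho 0.3), 71% and 82% (rho 0.5), and 89% and 93% (rho 0.7). Both fall and the ordering stays.

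**The case against.** Four points have weight.

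- **The model is labelled secondary.** True under Statistical analyses, whereas the power figures use the planning values of the primary composite. But the sentence covers the communicational assessments, the abstract presents the GEE as the analysis, and no other efficacy model is named. The label has to be reported; it does not remove the point.
- **The unconstrained mean model is inferred.** The article gives no mean structure or working correlation, and a condensed article may leave these to a fuller document. A GEE with a common baseline mean and a non-independence working correlation also yields a group-by-time effect and is about as efficient as covariate adjustment. If that is what is intended, stating it settles the matter. The usual reading of the wording is still a difference in change.
- **The simple formulas do not fit every outcome.** Perceived stress is measured seven times within each assessment and heart rate continuously. For these, a single post score regressed on a single baseline score is undefined without a summary measure.
- **The power figures in the table depend on independence and on an unknown rho.** Clustering lowers both columns, and at rho 0.7 the gain is under 3 percentage points.

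Two stronger readings are tempting. A reader might infer that the planned analysis is biased; under randomisation it is not, and any over-correction is conditional on the imbalance that happens to occur. A reader might also take the independent conditions literally and conclude that the trial has only 55% power. That is the rho = 0 row, but the article reports no correlation, and the phrase describes how the sample size was derived. It does not show that two scores from the same physician are uncorrelated.

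**Conclusion.** The point holds as one of efficiency. On its usual reading, the only named efficacy model uses the less precise of two valid contrasts, although the data for the better one are already collected before randomisation. For independent physicians and equal variances, baseline adjustment cuts the variance by 35% at rho 0.3, 25% at 0.5 and 15% at 0.7, and raises power by about 16, 9 and 3 percentage points. Above rho of about 0.8 the gain is small.

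The practical consequence is for the stated 80% power. With 60 independent physicians, the change contrast reaches it only if rho is at least about 0.5, whereas the adjusted analysis reaches it at any rho from 0 upwards. With trio clustering that guarantee no longer holds for either analysis (75% for the adjusted one at rho 0.3 and an assumed intraclass correlation of 0.1), but the advantage remains. The change is worth making; the plan is not invalid without it.

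**What to change.** State the treatment of baseline in the analysis wording:

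- For the primary communication composite, and for secondary outcomes with one baseline and one post score, analyse the post score on arm with the baseline score as covariate. Alternatively, fit the GEE with a common baseline mean across arms and a non-independence working correlation.
- For outcomes measured repeatedly within an assessment (perceived stress, heart rate), use the constrained-baseline model or adjust for a prespecified baseline summary.
- In every case, account for the training trio.
- Choose one of the two forms for the primary composite in advance. They treat physicians without a post score differently, and 20% drop-out is planned for.

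The cost is one residual degree of freedom and a few lines of analysis-plan text. No extra data, visits or participants are needed.
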